#### 2.4.3. Second Study Phase

Both patients who already participated in the first study phase and newly recruited patients can participate in the second study phase. Once drug specific conversion factors have been determined, in line with the real-world design of the study, participants will be able to choose between three TDM blood sampling options: (i) venous blood sampling at the treatment center, (ii) capillary blood sampling at the treatment center, and (iii) capillary blood sampling at home. In option (iii), patients send their capillary blood samples to the bioanalytical laboratories via normal post. After quantification of the drug concentrations in capillary blood, the corresponding drug concentrations in venous plasma are derived by applying the conversion factors determined in the first study phase. To assess the practicability of home-based capillary blood sampling, patients will be asked to complete a short questionnaire on their home-based blood sampling experience, e.g., if they experienced any problems, if they would be willing to use home-based capillary blood sampling again, and which blood sampling technique they would prefer in the future. The home-based collection of capillary blood will allow for samples to be sent to the bioanalytical laboratories in advance of patients’ next control visits, allowing the interpreted results to be ready for discussion at the time of the patients’ next visits.

#### 2.4.4. Toxicity Assessment

PRO-CTCAE questionnaires are integrated into the patients’ diaries and are asked to be completed once per month to assess the patients’ symptom burden. The PRO-CTCAE questionnaire used in this study was developed using the linguistically validated German PRO-CTCAE item library [36,37]. A total of 27 questions regarding the severity, frequency, presence or absence, and interference of adverse drug reactions categorized as “very common” or “common” in patients treated with either axitinib or cabozantinib [38,39] were selected for the questionnaire. Furthermore, patients can mention additional adverse drug reactions which are not specifically asked for in the 27 questions. Simultaneously, the patients’ symptom burden is graded using CTCAE version 5.0 [25] once per patient visit.

#### 2.4.5. TDM Result Report

Date and time of blood sample collection as well as date and time of last drug intake are documented for each patient. In absence of concentration thresholds which should not be exceeded for acceptable toxicity, the measured plasma concentrations are evaluated with respect to the expected concentrations at the time of blood collection after the last dose considering a patient’s individual covariates: For this, previously published nonlinear mixed-effects pharmacokinetic models of axitinib [40] and cabozantinib [41] are used to simulate concentration-time profiles using the patient’s dosing regimen and significant covariates (age, sex, body weight [40,41]) as model input. Stochastic simulations (*n* = 1000) are performed and the 90% prediction intervals (PI) as well as the interquartile range (IQR) together with the measured drug concentration are represented graphically. Depending on the individual drug concentration with respect to the 90% PI and the IQR, a dedicated TDM result summary will be added to the report (Figure 2):

**Measured drug concentration is within the IQR** (A): The measured concentration is in the *x*th (25th–75th) percentile of the concentrations that can be expected for axitinib/cabozantinib, considering the dosing regimen and relevant covariates of the patient. Thus, the risk of adverse drug reactions is low at the current dosing regimen.**Measured drug concentration is within the 90% PI but higher than the IQR** (B)**:** The measured concentration is in the *x*th (76th–95th) percentile of the concentrations that can be expected for axitinib/cabozantinib, considering the dosing regimen and relevant covariates of the patient. Due to the elevated concentrations, the patient should be carefully monitored to detect severe adverse drug reactions early on.**Measured drug concentration is within the 90% PI but lower than the IQR** (C)**:** The measured concentration is in the *x*th (5th–24th) percentile of the concentrations that can be expected for axitinib/cabozantinib, considering the dosing regimen and relevant covariates of the patient. Thus, the risk of adverse drug reactions is low at the current dosing regimen.**Measured drug concentration is higher than the 90% PI** (D)**:** The measured concentration is in the *x*th (>95th) percentile of the concentrations that can be expected for axitinib/cabozantinib, considering the dosing regimen and relevant covariates of the patient. Thus, a risk of adverse drug reactions is increased at the current dosing regimen and the patient should be carefully monitored.**Measured drug concentration is lower than the 90% PI** (E)**:** The measured concentration is in the *x*th (<5th) percentile of the concentrations that can be expected for axitinib/cabozantinib, considering the dosing regimen and relevant covariates of the patient. Thus, according to the result, the patient would not be adequately treated with axitinib/cabozantinib and further investigation for the cause is recommended. Possible causes include a delayed absorption of the drug, non-adherence, drug–drug interactions, or inaccurate documentation of the sample collection time.

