## 2. Materials and Methods

The ON-TARGET study (short for: Non-interventional study on Therapeutic Drug Monitoring (TDM) in patients with renal cell carcinoma and on the feasibility of using Volumetric Absorptive Microsampling (VAMS) for sample collection) is a prospective, multicenter, non-interventional study (DRKS00025325). Both hospitals and outpatient oncology practices which have implemented TDM as part of their clinical routine can participate as clinical study centers. Patient treatment and prescription of anticancer drugs is at the physician’s discretion and independent from a potential inclusion into the ON-TARGET study. Physicians may propose participation in the ON-TARGET study to (i) patients who experience, or are at high risk of experiencing, frequent and/or severe adverse drug reactions, or (ii) patients for whom TDM could be useful for other reasons (e.g., in the context of suspected non-adherence). The duration of the study participation is at the discretion of the patient and the treating physician.

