### 2.3. Secondary Objectives

Secondary objectives of the study are to identify patient subgroup(s) that experience particularly severe and/or frequent adverse drug reactions. Considering the reported exposure-toxicity relationship for both axitinib [31] and cabozantinib [32], potential plasma concentration thresholds for acceptable toxicity will be explored. Moreover, the feasibility and practicability of using VAMS capillary blood instead of venous blood as matrix for TDM will be investigated.

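### Report categories A and C tell the physician that the risk of adverse drug reactions is low, but a percentile at the patient's own regimen, with no toxicity threshold, supports only a relative statement

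*Protocol article*

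**What the plan says.** Section 2.4.5 explains how a measured concentration is interpreted. "In absence of concentration thresholds which should not be exceeded for acceptable toxicity", it is compared with the concentrations expected at that time after the last dose. These come from 1000 stochastic simulations of published pharmacokinetic models, with the patient's "dosing regimen and significant covariates (age, sex, body weight [40,41]) as model input".

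The result falls into one of five categories, each with a fixed summary text:
- A (25th to 75th percentile) and C (5th to 24th) carry the same conclusion: "Thus, the risk of adverse drug reactions is low at the current dosing regimen".
- B (76th to 95th) speaks of elevated concentrations and asks for careful monitoring.
- D (above the 95th) says: "Thus, a risk of adverse drug reactions is increased at the current dosing regimen".
- E (below the 5th) says that treatment would not be adequate and recommends looking for a cause.

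Section 2.3 refers to a reported exposure-toxicity relationship for both drugs and says that "potential plasma concentration thresholds for acceptable toxicity will be explored". Under Section 2.4.1 the interpreted result goes back to the treating physician within one week.

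**The concern.** The conclusion in A and C is introduced as following from the percentile, but it is a statement about the level of risk. The percentile says only where the patient stands among simulated patients with the same regimen and covariates. If a regimen caused reactions in most patients who take it, a patient at its median would still receive the A text.

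The report is meant to inform care. Section 2.5 has the centers state whether they changed the regimen because of the last monitoring result, and gives a concentration in the desired range as an example of a reason for not changing it. One of the two recruitment routes in Section 2 is "patients who experience, or are at high risk of experiencing, frequent and/or severe adverse drug reactions". For such a patient, a statement that risk is low can contradict the reason for enrolment. What is at stake is safety reassurance that the method cannot support. No endpoint, comparison or error rate is affected.

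**Working it through.** The plan states no figure on this point, so there is none to reproduce. The check is a reading of the text followed by two short calculations.

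**1. What the percentile can support.** The inputs are all in Sections 2.3 and 2.4.5: the reference distribution is conditional on the patient's own regimen, age, sex and weight; no threshold for acceptable toxicity exists; an exposure-toxicity relationship is reported for both drugs.
- *Category A.* The concentration lies in the middle half of what the regimen produces. With a monotone exposure-toxicity relationship, the risk is about what is usual for that regimen. Nothing in the protocol shows that this usual risk is low. The questionnaire in Section 2.4.4 is built from "adverse drug reactions categorized as “very common” or “common” in patients treated with either axitinib or cabozantinib". Those labels give no rates, so they do not show the risk to be high either.
- *Category C.* Exposure is below usual, so risk is probably below usual for the regimen. Low in absolute terms does not follow.
- *Category D.* The same scale is described with a relative word, increased. A and C use an absolute one.

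**2. Share of the expected distribution that carries the sentence.** From the printed cut-points, treated as continuous:
- A: 75 − 25 = 50%
- C: 25 − 5 = 20%
- A + C = 70%

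If the pharmacokinetic model is calibrated, this holds at any dose and any true toxicity rate, because toxicity does not enter the calculation.

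**3. Illustration with assumed inputs.** The documents give no risk of adverse reactions by regimen and no slope, so both are assumptions. Let z be the standardised log concentration at the patient's regimen, z ~ N(0,1), and

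P(reaction | z) = 1 / (1 + exp(−(a + ln(OR)·z))),

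with a solved so that the mean risk over z equals p. The risk is then averaged over the 25th to 75th percentile (A) and the 5th to 25th (C).

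| Average risk p | Risk in A (OR per SD 1.5 / 2 / 3) | Risk in C (OR per SD 1.5 / 2 / 3) |
|---|---|---|
| 5% | 4.7 / 4.2 / 3.3% | 3.1 / 2.0 / 1.0% |
| 10% | 9.5 / 8.7 / 7.2% | 6.3 / 4.3 / 2.2% |
| 20% | 19.4 / 18.3 / 16.2% | 13.4 / 9.5 / 5.5% |
| 40% | 39.7 / 39.1 / 38.1% | 29.9 / 23.4 / 16.0% |
| 60% | 60.3 / 60.9 / 61.9% | 49.7 / 42.8 / 34.1% |

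For p of 20% to 60%, the risk in A is 0.81 (16.2/20) to 1.03 (61.9/60) times the regimen average, and in C 0.28 (5.5/20) to 0.83 (49.7/60) times. For p of 5% to 10%, A falls to between 0.66 (3.3/5) and 0.95 (9.5/10) times the average. With a steep slope and a rare reaction, the upper tail pulls the average above the risk in the middle of the distribution.

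The table shows that the absolute risk in A is set mainly by p. The percentile says nothing about p, and the protocol does not give it.

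**The case against.** The best defence is that the sentence is relative in context. Each summary first gives the patient's percentile for the regimen and covariates, the value is plotted against the simulated intervals, and the sentence ends by referring to the current regimen. A physician may read low as one step on a five-level exposure scale and take it to mean no excess risk from exposure. That reading is fair for C. It does not work for A, where a concentration around the median means usual risk, and A and C share one sentence.

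It can also be said that the outcome is undefined and that for rare severe reactions the word may be true. This stands: with an assumed average risk of 5% to 10%, the risk in A is about 3% to 10%. But the sentence names no grade, and the protocol does not say which range applies.

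The third argument is that little harm can follow. No formal dose recommendation is made (Section 2.4.1), dose changes are the physician's decision (Section 3), and toxicity is graded at each visit and reported monthly by the patient (Section 2.4.4). This also stands and limits the weight of the point. It does not make the statement supported.

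Two stronger readings are tempting. A reader might infer that 70% of the 30 to 40 patients per drug, that is 21 to 28, will be told that their risk is low. The documents do not support that as a forecast. Patients recruited for toxicity may have higher concentrations than expected, which moves them towards B and D, and those recruited for suspected non-adherence may have lower ones, which moves them towards C and E. A reader might also infer that patients with an A report have a high absolute risk. The documents give no rate from which to say so.

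**Conclusion.** The point holds as one about wording: the conclusion in A is unsupported, and in C it goes further than the evidence. The supported statements are about the usual risk for the regimen in A, and below-usual exposure with probably below-usual risk in C.

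The only size that rests on the protocol's own numbers is the 70% of the expected distribution covered by A and C. It assumes a calibrated pharmacokinetic model and is a property of the cut-points. The statement about risk in C also relies on the reported exposure-toxicity relationship. All absolute risks in the table rest on assumed inputs and only illustrate the argument. The correction is worth making because the text goes to treating physicians and costs almost nothing to change, although the practical harm is limited.

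**What to change.** Replace the risk sentence in two of the report texts in Section 2.4.5:
- **A:** *Exposure is as expected for this regimen and these covariates; there is no sign of increased exposure-related risk.*
- **C:** *Exposure is lower than usual for this regimen; exposure-related risk is probably below average for this regimen.*
- **Add to both:** *No toxicity threshold is established, so this does not by itself indicate a low risk of adverse drug reactions.*

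Leave the texts of B, D and E, and the monitoring prompts in B and D, as they are. No new data, simulation or analysis is needed. The cost is report text that is slightly longer and less definite.

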### 2.5. Statistics

Based on the exploratory nature of the study, no formal sample size calculations were performed and no formal statistical considerations were made. In general, 30–40 patients per study drug are planned to be included. This number was derived from previous in-house studies, which showed that 30–40 sample pairs (i.e., simultaneous venous and capillary blood sampling) are optimal to identify reliable conversion factors for the calculation of venous drug concentrations from concentrations quantified in capillary blood samples. The usefulness of the TDM will be judged by the participating clinical study centers who are asked to rate the usefulness of the previous TDM on a scale from ‘very helpful’ via ‘somewhat helpful’ and ‘not really helpful’ until ‘not helpful at all’ at each study visit starting from the second visit after the baseline visit. In addition, the study centers are asked if they changed the dosing regimen based on the last TDM result and if yes, in which way (e.g., dose increase or decrease and increase or decrease of the dosing interval). If the dosing regimen was not changed, the study centers are asked to indicate why (e.g., the measured concentration was in the desired range, adverse drug reaction or other). At the end of a patient’s study participation, the study centers are asked to rate the overall usefulness of the TDM for the patient’s treatment. In the second study phase, the proportion of not adequately filled MITRA-VAMS^TM^ devices will be assessed and evaluated. In addition, the duration of shipment and the proportion of lost home-collected VAMS samples will be recorded.

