There are several challenges associated with the successful implementation of a TDM process: First, in many situations it is obvious that attaining a certain target concentration is needed to achieve the optimal effect. However, in most cases there is no formal proof that performing a TDM would be beneficial, which often prevents it from being recommended in treatment guidelines. An important reason for this is that prospective randomized controlled studies would have to be performed to provide this proof, and funding for such studies is rarely available. Second, considering the often-missing clear guidelines for when to perform TDM, the added value of a TDM in certain situations, e.g., in case of high toxicity or suspected non-adherence, has to be recognized individually by the treating physician. Third, the blood samples for drug concentration quantification have to be obtained and processed correctly. Sufficient blood volumes must be collected, which can be challenging especially for the capillary blood sample. Fourth, the blood samples have to be shipped to the bioanalysis centers and be analyzed within a short time frame. Fifth, efficient and sensitive bioanalysis methods have to be available. Finally, the evaluation and interpretation of the TDM results has to be quick, concise, and useful. In many cases, no PK target for efficacy and/or toxicity is available yet [2,3,61]. For these drugs, the mean/median exposure identified from other studies [2,61] in conjunction with the expected individual expected exposure based on patient’s covariates could be used until a PK target is available.

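### The report texts for bands A and C state a low risk of adverse reactions, but a percentile taken at the patient's own regimen supports only a statement about relative exposure

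*Protocol article*

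**What the plan says.** Section 2.4.5 of the protocol article (TDM Result Report) starts from the fact that there is no toxicity limit to compare with: "In absence of concentration thresholds which should not be exceeded for acceptable toxicity, the measured plasma concentrations are evaluated with respect to the expected concentrations". The expected concentrations come from 1000 stochastic simulations of a published pharmacokinetic model, run at the patient's own dosing regimen with age, sex and body weight as covariates. The result falls into one of five bands, and each band has a fixed summary text. Band A (25th to 75th percentile) and band C (5th to 24th percentile) end with the same sentence: "Thus, the risk of adverse drug reactions is low at the current dosing regimen". Band B speaks of elevated concentrations and asks for careful monitoring. Band D says the risk is increased. Band E points to inadequate treatment and lists possible causes.

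Three other places bear on this sentence:

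- Section 2.3 (Secondary Objectives) cites an exposure-toxicity relationship for both drugs and says that "potential plasma concentration thresholds for acceptable toxicity will be explored".
- Section 3 (Discussion) says that, for drugs without a target, mean or median exposure from other studies together with the exposure expected for the individual "could be used until a PK target is available".
- Section 2 (Materials and Methods) lets physicians propose the study to "patients who experience, or are at high risk of experiencing, frequent and/or severe adverse drug reactions".

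**The concern.** The closing sentence of bands A and C is a statement about clinical risk, yet the calculation behind it contains no toxicity information. It compares a concentration with other concentrations expected on the same regimen. The thresholds that could turn a concentration into a risk statement are among the things the study sets out to explore, so the report states a conclusion that the study has not yet reached.

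The report is what the study returns to the treating physician, and the primary objective is to reduce adverse reactions. A physician who reads that the risk is low may be reassured by a result that cannot carry that meaning. This matters most when no reaction is yet visible, for example at the first sample after a dose increase, because the clinical picture then offers nothing to set against the text.

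**Working it through.** The plan gives no figure behind the sentence, so there is none to reproduce. The check asks what the percentile can establish.

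**1. Inputs to the report text (Section 2.4.5).** These are the measured concentration, the times of dose and sample, the regimen, age, sex and body weight, and a pharmacokinetic model. No toxicity model, reaction rate or concentration limit is named as an input.

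**2. What the exposure-toxicity relationship adds (Section 2.3).** If toxicity rises with exposure, then within one regimen the risk in C is no higher than in A, and the risk in A no higher than in B or D. That is an ordering. A concentration in the middle of the distribution implies roughly the typical risk of that regimen. Whether the typical risk is low is a separate question. Section 2.4.4 builds the patient questionnaire from reactions classed as very common or common with these drugs, so typical cannot simply be equated with low.

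**3. What the provisional comparator adds (Section 3).** It justifies expected exposure as the yardstick until a target exists. It does not say that lying near the yardstick means low risk.

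**4. The share of the reference distribution that carries the sentence.**

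- Band A: 0.75 − 0.25 = 0.50
- Band C: 0.25 − 0.05 = 0.20
- Together: 0.50 + 0.20 = 0.70

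This 70% is fixed by the band limits, whatever the dose and whatever the true reaction rate. It equals the expected share of reports only if the enrolled patients' concentrations follow the simulated distribution.

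**5. What happens when the dose changes.** Let X be the simulated concentration at the current dose and c the patient's measured value. Assume dose proportionality, which the documents do not state. If the dose is multiplied by r, the reference becomes rX and the patient's value becomes rc. Then

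P(rX < rc) = P(X < c).

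The percentile, the band and the closing sentence are unchanged, although the concentration is r times as high. This holds for any spread of the distribution. If toxicity rises with exposure, as Section 2.3 reports, the risk has risen and the text has not registered it.

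**6. Who may receive the text (Section 2).** A patient may be enrolled because reactions are already present. Nothing in the band rule prevents that patient's concentration from falling in A or C, so the report could call the risk low while reactions are under way. The documents give no reaction rate by band or by concentration, so the frequency of this cannot be derived.

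**7. The wording of the bands side by side.** Band D uses a comparative term, increased. Bands A and C use low, without a comparison, and give the same sentence to the middle half of the distribution as to the range below it.

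**The case against.** The best defence is that the sentence is meant relatively. It ends by referring to the current regimen, it follows a percentile that is explicitly conditional on that regimen, and it sits in an ordered set of texts in which D says increased. On that reading, low means only that excess exposure has not raised the risk. The physician also sees the percentile and the plot and knows the dose. The reading is possible, but it is not what the text says. Naming the regimen tells the physician at which dose the risk is called low; it does not turn low into not raised.

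The ordering of the bands has support. Section 1 links supratherapeutic concentrations, in approximately 15% of patients, with increased toxicity, and Sections 2.3 and 3 point the same way. That part of the defence stands, but it goes no further than a relative statement.

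The consequences are also limited, and this stands too. Toxicity is "graded using CTCAE version 5.0 [25] once per patient visit", and patients complete the questionnaire monthly whatever the band. No formal dose recommendation is made, and Section 3 leaves every dosing decision to the physician. The article condenses the protocol and does not show the whole report template, so an added caveat cannot be excluded.

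A reader might infer from Section 2.5 that dose increases are expected after a TDM result, so that step 5 describes a usual course of events. The section does not support this. It asks centres "if they changed the dosing regimen based on the last TDM result and if yes, in which way (e.g., dose increase or decrease", and asks for the reason when nothing was changed. It predicts neither the frequency nor the direction of changes. Step 5 shows a property of the method, not how often it comes into play.

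**Conclusion.** The point holds as a wording error in two fixed report texts and deserves consideration. The documents support saying that exposure is not higher than expected for the regimen. They do not support saying that the risk of adverse reactions is low. This conclusion needs no numerical assumption, because it follows from the absence of any toxicity input and of any threshold. The unchanged text after a dose change additionally assumes dose proportionality.

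A reader might go further and infer that 70% of reports will mislead. The documents do not support that. Section 2 allows enrolment because of reactions, which could shift patients towards B and D, or because of suspected non-adherence, which could shift patients towards C and E. The share of A and C reports is therefore unknown, as is the share issued to patients with ongoing reactions. Nor can a risk be put on the sentence by way of the width of the bands, because the documents do not give the concentration variability.

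**What to change.** In Section 2.4.5, keep the percentile sentence in both texts and replace only the closing sentence.

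- Band A: *Exposure is not higher than expected for this regimen and these covariates.*
- Band C: *Exposure is lower than typically expected for this regimen and these covariates.*
- Both then continue: *This alone does not establish a low risk of adverse drug reactions; toxicity must be judged clinically.*

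The first part partly restates the percentile, but it keeps A and C distinct from each other and from B. The caveat is the substantive change.

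The cost is one closing sentence in each of two templates. It needs no new data and gives no dosing advice, so it fits the non-interventional design. The drawback is that the wording is slightly less directive. If the full template already carries an equivalent caveat, the closing sentence should still be changed so that the two do not conflict.

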The ON-TARGET study focuses on the potential of routine TDM to reduce the frequency and severity of adverse drug reactions experienced during oral tumor therapy. There are several additional possible endpoints with regards to the potential of TDM that could and should be addressed in dedicated follow-up studies: first, considering that approximately 30% of patients are underdosed at the recommended standard dose, efficacy is a highly relevant endpoint. Investigating the potential of routine TDM to increase efficacy using hard endpoints (such as overall survival) with sufficient power requires large sample sizes and long follow-up times, also as overall cancer prognoses improve with new treatments. A less cost-intensive option is to focus on surrogate endpoints, e.g., the reduction of the frequency of patients with drug exposure below the TDM target, as it is done in the Dutch DPOG-TDM study [5]. Of note, even though it is often possible to increase drug exposure with cost-neutral interventions [13,14,62,63], using TDM to optimize efficacy will usually also require dose escalations. These dose escalations can lead to the prescription of off-label doses, which should be considered and accounted for early on when selecting an appropriate study design (e.g., interventional, non-interventional). Another endpoint of high relevance is the improvement of treatment adherence and the detection of non-adherence. According to recent literature, non-adherence to targeted oral anticancer drugs is frequent [64,65,66,67,68] and a serious risk factor for treatment failure [69]. Routine TDM may allow the early identification of treatment non-adherence as indicated by drug concentrations significantly lower than expected for a given patient and dosing regimen. For example, in a recent prospective study applying a pharmacokinetic threshold for non-adherence, one in six breast cancer patients receiving tamoxifen was found to be non-adherent [70]. Given the prevalence of non-adherence in targeted oral anticancer drug treatment of 29–59% [67], the potential of routine TDM to identify non-adherence early on should be further investigated in prospective studies.

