**Figure 2 cancers-13-06281-f002:**
[figure not shown]
Stochastic simulations for an exemplary axitinib concentration-time profile. Green area: 50% prediction interval (25th–75th percentile), grey area: 90% prediction interval (5th–95th percentile). Letters (A–E) are explained in Section 2.4.5 in the main text.

**Table 1 cancers-13-06281-t001:** Overview of the data collected and the time of collection in the ON-TARGET study.

Data Collection Parameter	Baseline Visit	Follow-Up Visits	Continuous
Vital parameters	X	X	
Information on current tumor therapy (treatment setting, current medication, concomitant treatment)	X	X	
Information on previous tumor therapies	X		
Information on tumor diagnostics	X	X ^1^	
Tumor classification according to TNM	X	X ^1^	
Concomitant diseases	X	X ^2^	
Current supportive medication	X	X ^2^	
Current comedication	X	X ^2^	
Toxicity according to CTCAE 5.0	X	X ^2^	
Symptomatic toxicity according to PRO-CTCAE			X ^3^
Drug intake			X ^4^
ECOG performance status	X	X	
Clinical chemistry parameters	X	X	
If applicable, information on the treatment termination (Date, reason(s))		X	

^1^ Only if tumor staging was performed; ^2^ Only if changes occurred since the last visit; ^3^ Filled in once monthly by the patient. ^4^ Filled in daily by the patient. Abbreviations: CTCAE: Common Terminology Criteria for Adverse Events; PRO: patient-reported outcomes; ECOG: Eastern Cooperative Oncology Group; TNM: tumor (T), nodes (N), metastasis (M).

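### The band-E report text infers inadequate treatment from a percentile that shows only a lower-than-expected concentration

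*Protocol article*

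**What the plan says.** Section 2.4.5 builds the reference for each report from 1000 stochastic simulations of published population pharmacokinetic models, "using the patient’s dosing regimen and significant covariates (age, sex, body weight [40,41]) as model input". The measured value is shown with the simulated 90% prediction interval and the interquartile range. The caption of Figure 2 gives the limits of the 90% interval as the 5th and 95th percentiles.

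Band E is a value below the 90% interval. Its text first gives the percentile (under the 5th) among concentrations that can be expected for that regimen and those covariates. It then concludes that "according to the result, the patient would not be adequately treated with axitinib/cabozantinib and further investigation for the cause is recommended". The causes offered begin "Possible causes include a delayed absorption of the drug, non-adherence" and go on to drug interactions and a wrongly documented sampling time. Ordinary variability is not named.

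Section 2.4.5 explains that expected concentrations are used because no concentration limit for acceptable toxicity exists. It names no efficacy threshold for either drug. The Discussion (Section 3) says of oral anticancer drugs in general: "In many cases, no PK target for efficacy and/or toxicity is available yet". It also describes how monitoring may identify non-adherence, "as indicated by drug concentrations significantly lower than expected for a given patient and dosing regimen".

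**The concern.** Band E draws a conclusion about treatment adequacy from a position in a distribution. That distribution describes patients on the same documented regimen with the same covariates, so its lower tail is part of what the model expects. Falling in the tail is uncommon, but it does not in itself show that the dose is inadequate or that something has gone wrong. Two things are missing for the conclusion to follow: a concentration below which efficacy is known to suffer, and an acknowledgement that some values fall there through normal variability.

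This is wording that the treating physician receives. Under Section 2.5 the centres then record whether they changed the regimen because of the last result, and they rate how useful the monitoring was. An unsupported label can therefore reach both the clinical response and the study's own data on usefulness.

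**Working it through.** **Inputs.** A 90% prediction interval with 5th and 95th percentile limits (Section 2.4.5, Figure 2); 1000 simulations (Section 2.4.5); 30 to 40 patients per drug (Section 2.5); one sample pair per patient assumed in the first phase (Section 2.4.2). The number of samples per patient over the whole study is not stated.

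**1. Size of band E.** Lower tail = (1 − 0.90)/2 = 0.05. This reproduces the document's own limit, below the 5th percentile.

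**2. Expected band-E results at one sample each**, if every patient is dosed and sampled as documented and the model is calibrated:
- 30 patients: 30 × 0.05 = 1.5; chance of at least one = 1 − 0.95^30 = 78.5%.
- 40 patients: 40 × 0.05 = 2.0; chance of at least one = 1 − 0.95^40 = 87.1%.
- Both drugs, 60 to 80 patients: 3 to 4 expected; chance of at least one 95.4% to 98.3%.

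**3. Repeated samples (illustration).** The sample counts and correlations here are assumptions. Chance that one such patient has at least one band-E report:
- 3 samples: 1 − 0.95^3 = 14.3% if independent; about 9% by simulation with a within-patient correlation of 0.8.
- 6 samples: 1 − 0.95^6 = 26.5% if independent; about 13% by simulation with a correlation of 0.8.

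Independence gives the upper end, because samples from one patient tend to be alike.

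**4. How firm the 5% is.** With 1000 simulations, the true probability below the simulated 5th percentile has a Beta(50, 951) distribution, with a 95% range of 3.7% to 6.4%. The article does not say whether the interval includes residual error. If it did not, the tail would be Φ(−1.645 × ω/√(ω² + σ²)), where ω is the between-patient and σ the residual SD on the log scale. Assuming σ = ω/2 gives 7.1%; assuming σ = ω gives 12.2%.

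**5. Does the percentile bear on adequacy?** The regimen is an input to the simulation, so the interval moves with the regimen. If concentrations rise and fall roughly with dose (an assumption), the 5th percentile is a lower concentration on a lower dose. One concentration can then be in band E on one regimen and inside the interval on another. A limit that shifts in this way cannot stand in for a fixed efficacy threshold. Nor does it match the general figure in the Discussion that about 30% of patients are underdosed at the standard dose: the band from the 5th to the 24th percentile carries no adequacy message at all.

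**The case against.** The strongest reply is that a low value arising from normal variability may be genuine underexposure. The Introduction reports up to 30% of patients with subtherapeutic concentrations, and finding such patients is what monitoring is for. This stands. A reader might infer from the 5% that a fixed share of correctly treated patients is labelled inadequately treated. The documents do not support that, because being dosed as documented is not the same as being adequately treated. The point is narrower: the percentile does not settle the matter either way.

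Other parts also stand:
- The sentence is hedged, and the physician sees the percentile and the plot.
- The list of causes is open, and delayed absorption can itself be ordinary variability.
- Section 2.1 admits any comedication and Section 2 invites patients with suspected non-adherence, so the observed share in band E need not be 5%.
- The Discussion's remark on missing targets is general, not specific to these two drugs.

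A reader might also infer that each sample is judged alone, or that the study cannot learn whether band E carries information. Neither is shown. The article does not say whether later reports display earlier results. Band E is not an endpoint, the results and diaries are stored, and a table of observed against expected shares is something an analysis plan may contain.

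None of this repairs the sentence itself. Hedging does not supply the missing efficacy reference, and an open list still leaves out the explanation that the interval's own definition implies.

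**Conclusion.** The point holds as a fault of inference in the report text. A value below the 90% prediction interval shows that the concentration is lower than expected for the patient's documented regimen and covariates. Without a stated efficacy threshold it does not show inadequate treatment.

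About 5% of samples from patients dosed and sampled as documented are expected in band E, or 1.5 to 2 per drug at one sample each. This rests on published models that are calibrated for these patients and on an interval that includes residual variability; the article confirms neither. Repeated sampling raises the count by an amount the documents do not allow to be fixed.

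No study estimate or planned comparison is shown to change. The case for acting is that the message reaches physicians, can feed the regimen changes and usefulness ratings recorded under Section 2.5, and is easily corrected.

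**What to change.** Reconcile the band-E sentence in Section 2.4.5 with the definition of the prediction interval. The text should state that:
- the concentration is lower than expected for this regimen and these covariates;
- about 5% of samples from patients dosed and sampled as documented are expected there;
- normal between-patient and residual variability is among the possible explanations, beside those already listed.

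Either tie the statement on adequacy to a stated efficacy reference for the drug concerned, or remove it. Before printing the 5%, confirm that the simulated interval includes residual error.

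The cost is an edit to the report template. The small downside is a less directive message to the physician. No dose or clinical rule is proposed.
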